#### 2.6.3. Wearable Sensor System

Both members of the recruited dyads will wear, on the non-dominant wrist, the E4 wristband (Empatica Inc., [name]) which is a wearable research device that offers real-time physiological data acquisition through four sensors:A 3-axis accelerometer, which measures acceleration on three orthogonal spatial directions;A Galvanic Skin Response (GSR) sensor, which measures the electrical conductance of the skin;A photoplethysmography (PPG) sensor, which continuously measures Blood Volume Pulse (BVP, i.e., volumetric variations of blood circulation) using a light source and a photodetector at the surface of skin;A thermopile infrared sensor, which reads peripheral skin temperature.

Besides the four sensors, the E4 wristband is equipped with an event mark button, which can be used to tag events and link them to the recorded physiological signals. We will ask one member of each dyad (caregiver in patient-caregiver dyads and RCM in healthy control dyads) to use this button to mark events with supposed strong emotional charge for their partner. This information can indeed be useful to interpret and check the validity of the GSR and PPG signals.

The main instructions for the use of the E4 wristband (see Supplementary Materials, File S2 for more details on the instructions given to patient-caregiver dyads) are as follows: (1) wear the bracelets on the non-dominant wrist as often as possible during the daytime and nightime; (2) keep the smartphones with you as often as possible (for data retrieval from E4 bracelets to smartphones); (3) beware of avoiding the exchange of your bracelet with your partner’s; (4) charge the battery of E4 bracelets every evening (approximative time of charge: one hour and a half).

#### 2.6.4. Questionnaire Interfaces on Smartphone Application

To collect all the active data from the questionnaires, a smartphone application (sending notifications) will be used by the caregiver (in patient-caregiver dyads). On this application, there will be two interfaces:−The day questionnaire interface will be used by one partner (caregiver in patient-caregiver dyads) one day per week to provide information on their partner’s behaviour at: (1) Bedtime (the day before); (2) Wake time; (3) Breakfast; (4) Lunch; (5) Dinner. This interface will also be used at the end of the day by the caregiver (only in patient-caregiver dyads) to provide their perception of the dyad’s psychological status (i.e., patient’s apathy, perceived burden and quality of life) during the day.−The month questionnaire interface will be used by the caregiver (only in patient-caregiver dyads) at T0 + 28 days to complete the three validated questionnaires (AS, ZBI, SF-36) on their global perception of the dyad’s psychological status (i.e., patient’s apathy, perceived burden, and quality of life) during the 28 days of follow-up.

### 2.7. Data Flow

All the information collected during Visit 1 will be registered using REDCap^®^ (version 10.9.4) secure web application. These data will be stored on the local secure server (of Paris Brain Institute, Paris, France).

During the 28-day follow-up, remote data collection will require two steps (see Figure 4):Collection of two types of data through an application installed (by the investigators) on patients’ and caregivers’ smartphones: data from sensors (passive behavioural data), and data from questionnaires (active behavioural data + caregiver’s perception of the dyad’s psychological state);Transfer of these data to a remote server application hosted by a local secure server (of the Paris Brain Institute).

Data from the sensors of the E4 bracelet will be continuously collected in both partners of the dyad and transferred to their smartphone application in real-time, each bracelet being paired with its carrier’s smartphone. In case of connection loss with the paired bracelet, the application will send a push notification to warn the participant. Data from questionnaires will be collected directly through the application, sending reminder notifications to the caregiver in patient-caregiver dyads (or to one of the partners, randomly selected, in control dyads).

After being encrypted, all the data collected by the application will be temporarily stocked on the smartphone and progressively transferred to the remote server application hosted by the local secure server. All the data collected by the application will be anonymised and identified only through the associated time-stamp and individual PIN code attributed to each participant of the study.

### 2.8. Statistical Analyses

#### 2.8.1. Sample Size

The required sample size is estimated according to our primary objective of validation of a measurement model for the three assumed behavioural markers of apathy. We will use a Confirmatory Factor Analysis (CFA) based on Structural Equation Modelling and according to Westland [49]. For this kind of models, the required sample size depends on the ratio r = p/k where p is the number of observed indicator variables (i.e., the total number of metrics) and k is the number of unobserved latent variables in the model (i.e., the number of behavioural markers of apathy we want to measure through these metrics). Assuming that we can find 36 metrics for the measure of the three behavioural markers of apathy for one dyad, a ratio r = p/k = 36/3 = 12 would require a sample size of at least 50. We thus decided to recruit a total of 60 dyads, which is 20% more than this minimum sample size, to compensate for potential dropout of some dyads during follow-up. Besides, a total of 60 dyads seems to be a suitable sample size in terms of feasibility (given that we plan to complete the inclusions within a maximum of 24 months by recruiting 2 or 3 dyads per month). With this sample size (N = 60) for a model with p = 36 and k = 3 (591 degrees of freedom), the statistical power (i.e., the probability of rejecting the null hypothesis of a model with close fit when true model fit is mediocre) is quite satisfactory (π = 94.2%).

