#### 2.8.2. Analysis Plan for Primary Objective

First, we will extract the metrics from both passive and active behavioural data on a monthly and a daily basis for all dyads. Using these metrics, we will explore a measurement model for the three assumed behavioural markers of apathy on the two time-scales (with monthly scale metrics for the monthly scale model and daily scale metrics for the daily scale model).

We will use Exploratory Factor Analysis (EFA) and Confirmatory Factor Analysis (CFA) in order to identify the system of metrics organised between the three markers, which is the most adapted to measure them. Statistical criteria for the validation of the measurement model tested in CFA (i.e., Root Mean Square Error of Approximation < 0.08, Standardized Root Mean Square Residual < 0.08, Comparative Fit Index > 0.9, Tucker-Lewis Index > 0.9) will guarantee its good adjustment to the data. The internal consistency of the measures of the three behavioural markers will be assessed using Cronbach’s alpha (>0.70). The reliability of the measures (on a daily scale) will also be evaluated through the correlations between the behavioural marker scores obtained on four time-steps (once a week) during the 28-day follow-up (high correlation indicating high reliability).

We will compare the measurement models and mean scores on the three behavioural markers of apathy between groups of patient-caregiver dyads and control dyads (on two time-scales). We will demonstrate that the patient-caregiver dyad’s scores on the three assumed markers of apathy can predict the dyad’s psychological state (as perceived by the spouse caregiver) using linear regression models on the monthly and daily scales. In a perspective of precision medicine, we will also investigate the disentangling of different profiles of apathy, using clustering analyses from the calculated behavioural markers of apathy.

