Another potential measurement bias can be underlined in the assessment of behavioural markers of apathy through metrics from passive data of both individuals with dementia and their caregiver. Residual errors of prediction for the passive behavioural metrics aimed at measuring one behavioural marker will not be independent from each other and identically distributed: in particular, the residual errors relative to the caregivers’ metrics are likely to be covariates and so are the residual errors relative to the patients’ metrics. These covariances will have to be taken into account in the statistical modelling. It is also possible that the metrics extracted for both partners of one dyad are not sufficiently correlated to correspond to the measure of the same latent behavioural marker (especially for patient-caregiver dyads). If so, behavioural markers of apathy will need to be assessed using only the patient’s passive behavioural data instead of both the patient’s and caregiver’s passive behavioural data.

Finally, it seems difficult to estimate the extent of the measurement bias that might be introduced by the support provided to the caregiver through the study follow-up in an objective way. We could try to investigate a potential modification of signals from sensors worn by the caregiver between before and after a phone call with the investigator. However, we expect that this impact can be neglected (only two phone calls are scheduled with the investigator, and this is mostly for technical support).

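### The 94.2% power is computed on all 60 recruited dyads and all 36 assumed metrics, for a close-fit test the analysis plan does not use; at the plan's own minimum of 50 dyads it is 86.7%

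*Protocol article*

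**What the plan says.** Section 2.8.1 (Sample Size) starts from a rule on the ratio of metrics to latent markers. The metric count is an assumption: "Assuming that we can find 36 metrics for the measure of the three behavioural markers of apathy for one dyad". The ratio 36/3 = 12 "would require a sample size of at least 50" dyads. Recruitment is then set at 60, "which is 20% more than this minimum sample size, to compensate for potential dropout of some dyads during follow-up". The paragraph ends with power: "With this sample size (N = 60) for a model with p = 36 and k = 3 (591 degrees of freedom"), the probability of rejecting close fit "when true model fit is mediocre) is quite satisfactory (π = 94.2" per cent.

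Section 2.8.2 sets out how the measurement model will be judged. Exploratory and confirmatory factor analysis are used to find the best-suited set of metrics. The model is then held to four cut-offs: "Root Mean Square Error of Approximation < 0.08", SRMR below 0.08, and CFI and TLI above 0.9. Cronbach's alpha above 0.70 is required for internal consistency. No test of close fit is mentioned.

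Section 3.2 names dropout and poor compliance as the first limitation. It also provides a fallback if the two partners' metrics do not correlate enough: "behavioural markers of apathy will need to be assessed using only the patient’s passive behavioural data". It gives no number of metrics for that case. It adds that residual covariances will have to be modelled.

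**The concern.** The power figure rests on three conditions that the rest of the plan does not secure.

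- **Dyads.** The extra 10 dyads are allotted to dropout and then counted again as analysed dyads in the power calculation.
- **Metrics.** The degrees of freedom, and so the power, depend strongly on the number of metrics. The count of 36 is assumed, factor analysis may retain fewer, and the patient-only fallback removes the caregiver's passive metrics.
- **Rule.** The power belongs to a significance test of close fit, whereas the model will be accepted or not on fit-index cut-offs.

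A reader who sees a power above 90% described as quite satisfactory will take it as the study's ability to detect a poorly fitting measurement model, which is the primary objective. The figure does not describe that ability under the rule the plan applies.

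**Working it through.** **Inputs.** From section 2.8.1: N = 60 recruited, minimum 50, p = 36 metrics, k = 3 markers, "591 degrees of freedom". Not stated and therefore inferred: close fit as RMSEA 0.05, mediocre fit as RMSEA 0.08, alpha 0.05 in the upper tail. These are accepted because they reproduce the printed figure. The alternative RMSEA pairs tried (0.05/0.09, 0.05/0.10, 0.06/0.08, 0.08/0.10, 0/0.05) do not.

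**Degrees of freedom.** For three correlated factors, df = p(p+1)/2 − (2p + 3). With p = 36: 666 − 75 = 591, as printed.

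**Power formula.** The fit statistic is taken as noncentral chi-square with noncentrality (N − 1) × df × RMSEA². The critical value is the 95% quantile under RMSEA 0.05. Power is the probability of exceeding it under RMSEA 0.08.

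**Reproducing the plan's figure, N = 60.**
- Null noncentrality: 59 × 591 × 0.0025 = 87.2; critical value 743.8.
- Alternative noncentrality: 59 × 591 × 0.0064 = 223.2.
- Power = 94.2%. The printed figure is correct for these inputs.

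**At the plan's minimum, N = 50.**
- Null noncentrality: 49 × 591 × 0.0025 = 72.4; critical value 727.7.
- Alternative noncentrality: 49 × 591 × 0.0064 = 185.3.
- Power = 86.7%.

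**With fewer metrics.** The plan gives no count after factor analysis or after the fallback, so the rows below 36 are illustrations.

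| Metrics p | df | Power, N = 60 | Power, N = 50 |
|---|---|---|---|
| 36 | 591 | 94.2% | 86.7% |
| 30 | 402 | 84.6% | 73.9% |
| 24 | 249 | 67.8% | 56.5% |
| 18 | 132 | 46.2% | 37.6% |

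The row p = 18 is what results if the fallback halves the count. That is plausible for the monthly model, which section 2.4 builds from passive data only. It is too pessimistic for the daily model, where active metrics remain.

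**Residual covariances.** Each one modelled costs a degree of freedom. As an illustration, 100 of them at p = 36 leave 591 − 100 = 491 df and a power of 90.2% (N = 60) or 80.9% (N = 50).

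**Powered test against stated rule.** Section 2.8.1 powers a rejection of RMSEA 0.05 by a significance test. Section 2.8.2 compares a point estimate of RMSEA with 0.08 and adds three further indices. These are different procedures, and the power of one does not carry over to the other.

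**How far large-sample theory can be trusted here.** Two separate runs of maximum-likelihood factor-analysis simulations used p = 36 and three factors, with assumed loadings of 0.7 and factor correlations of 0.5. An exactly correct model met RMSEA below 0.08 in about 57% to 65% of samples at N = 60 and in 5% at N = 50. The nominal 5% close-fit test rejected that correct model in 83% to 90% of samples at N = 60 and in 98% to 100% at N = 50. The chi-square approximation behind 94.2% and 86.7% is therefore poor at this size.

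**The case against.** Much can be said for the plan, and most of it stands.

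- The 94.2% is not a miscalculation; it reproduces exactly.
- The power is not the only basis for the sample size. The minimum of 50 comes from the ratio of metrics to markers, and power is a closing remark. Correcting it does not by itself change the planned number.
- 86.7% is still above the usual 80%, so the dropout point alone is small.
- The metric count is openly called an assumption, and the fallback is disclosed as a limitation.

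A reader might also draw stronger conclusions that the documents do not support.

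- **That 60 dyads were claimed to cover a 20% loss.** The text says that 60 is 20% above the minimum, which is true (50 × 1.2 = 60). It states no dropout rate.
- **That the plan's own fallback has 38% to 46% power.** That range needs 18 remaining metrics, a number the plan does not give.
- **That a mediocre model would pass about half the time.** Large-sample theory does give 0.51 for an estimated RMSEA below 0.08 when the true value is 0.08. But this concerns one of four fit indices, and the theory fails at this sample size. In one of the simulations above (150 runs per setting), no sample with true RMSEA 0.08 met that cut-off at N = 50 or 60. Under those assumptions the danger is rejection of good models.
- **That the close-fit test, or the upper RMSEA limit, should become the criterion.** The simulated rejection rates for a correct model show that adopting the test would do harm, and a rule on the upper limit would be stricter than the present cut-off on the estimate.

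**Conclusion.** The point holds in a limited form. The quoted power applies to 60 analysed dyads, 36 retained metrics and a test of close fit. The plan itself expects to lose some dyads, may lose metrics, and uses another rule. On the same formula the power is 86.7% at 50 dyads, and it falls below 80% at 50 dyads once the count drops to 30 metrics (73.9%).

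These figures rest on the inferred RMSEA values and alpha, on illustrative metric counts, and on a large-sample approximation that the simulations show to be unreliable here. The simulations in turn depend on assumed loadings and factor correlations, so their percentages are indicative only. Severity is minor to moderate: the statement in section 2.8.1 is more favourable than the design supports, but the planned number of dyads is not shown to be wrong.

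**What to change.** In section 2.8.1:

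1. Quote the power at 50 evaluable dyads (86.7% for 36 metrics), and state the RMSEA values and alpha used.
2. Add the range over the number of metrics retained, labelled as assumptions, for example 73.9% to 84.6% for 30 metrics and 37.6% to 46.2% for 18 (50 and 60 dyads respectively).
3. Say that the figure is a large-sample approximation for a test of close fit and does not describe the decision rule of section 2.8.2.
4. Report by simulation, at 50 to 60 dyads, how often the joint rule on RMSEA, SRMR, CFI and TLI accepts a correct model and a mediocre one. State the loadings, factor correlations, residual covariances and metric counts assumed.

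The cost is a reworded paragraph and a short simulation. The stated power becomes less favourable. No extra dyads or data are proposed.

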#### 2.8.2. Analysis Plan for Primary Objective

First, we will extract the metrics from both passive and active behavioural data on a monthly and a daily basis for all dyads. Using these metrics, we will explore a measurement model for the three assumed behavioural markers of apathy on the two time-scales (with monthly scale metrics for the monthly scale model and daily scale metrics for the daily scale model).

We will use Exploratory Factor Analysis (EFA) and Confirmatory Factor Analysis (CFA) in order to identify the system of metrics organised between the three markers, which is the most adapted to measure them. Statistical criteria for the validation of the measurement model tested in CFA (i.e., Root Mean Square Error of Approximation < 0.08, Standardized Root Mean Square Residual < 0.08, Comparative Fit Index > 0.9, Tucker-Lewis Index > 0.9) will guarantee its good adjustment to the data. The internal consistency of the measures of the three behavioural markers will be assessed using Cronbach’s alpha (>0.70). The reliability of the measures (on a daily scale) will also be evaluated through the correlations between the behavioural marker scores obtained on four time-steps (once a week) during the 28-day follow-up (high correlation indicating high reliability).

We will compare the measurement models and mean scores on the three behavioural markers of apathy between groups of patient-caregiver dyads and control dyads (on two time-scales). We will demonstrate that the patient-caregiver dyad’s scores on the three assumed markers of apathy can predict the dyad’s psychological state (as perceived by the spouse caregiver) using linear regression models on the monthly and daily scales. In a perspective of precision medicine, we will also investigate the disentangling of different profiles of apathy, using clustering analyses from the calculated behavioural markers of apathy.

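### At 36 metrics and 50–60 dyads, the uncorrected fit cut-offs reject an exactly correct three-marker model in most samples unless loadings are very high, and the 94.2% power does not show that good and mediocre fit can be told apart

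*Protocol article*

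**What the plan says.** Section 2.8.1 of the protocol article sets the planning model: "Assuming that we can find 36 metrics for the measure of the three behavioural markers of apathy for one dyad", then "a ratio r = p/k = 36/3 = 12 would require a sample size of at least 50". Recruitment follows from that: "We thus decided to recruit a total of 60 dyads, which is 20% more than this minimum sample size", with the excess meant to cover dropout. For 36 metrics, three markers and 591 degrees of freedom at N = 60, the section reports a power of 94.2%, defined as "the probability of rejecting the null hypothesis of a model with close fit when true model fit is mediocre".

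Section 2.8.2 gives the criteria for validating the model tested in the confirmatory analysis: "Root Mean Square Error of Approximation < 0.08, Standardized Root Mean Square Residual < 0.08, Comparative Fit Index > 0.9, Tucker-Lewis Index > 0.9". It says that these "will guarantee its good adjustment to the data". Neither section names a small-sample correction or considers how often a correct model would meet the criteria.

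**The concern.** These cut-offs presuppose large-sample behaviour. The planned model has 75 free parameters, before the residual covariances that Section 3.2 says must be taken into account, and 60 dyads at most. With so few rows per metric, the maximum-likelihood chi-square runs above its degrees of freedom even when the model is exactly true. That raises RMSEA and lowers CFI and TLI. SRMR is separately enlarged by sampling error in the 630 correlations.

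If so, failing the criteria says little about whether the three-marker structure is wrong. It also creates pressure to remove metrics until the indices pass, in the same dyads. The stated power is affected too: a test that mostly rejects correct models will show high nominal power without separating good from mediocre fit.

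**Working it through.** **Inputs from the document.** p = 36, k = 3, N = 60 recruited, minimum 50, df = 591, power 94.2%, and the four cut-offs.

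**Assumptions.** RMSEA 0.05 for close fit, 0.08 for mediocre fit and a 5% level (not printed); standard maximum likelihood; equal loadings from 0.40 to 0.95; marker correlations from 0.3 to 0.8. For scale, Cronbach's alpha of 0.70 with 12 metrics implies a mean correlation of 0.70/(12 − 11 × 0.70) = 0.163, a loading of about 0.40. Loading 0.7 implies alpha 12 × 0.49/(1 + 11 × 0.49) = 0.92, and loading 0.8 implies 12 × 0.64/(1 + 11 × 0.64) = 0.955.

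**Step 1: the plan's own figures.**
- df = 36 × 37/2 − (36 loadings + 36 residual variances + 3 correlations) = 666 − 75 = 591. Reproduced.
- Power uses a non-central chi-square with non-centrality (N − 1) × df × RMSEA². At N = 60 this is 59 × 591 × 0.0025 = 87.17 under close fit and 59 × 591 × 0.0064 = 223.16 under mediocre fit. The 5% critical value is 743.77 and the power is 0.942. Reproduced.
- At N = 50 the non-centralities are 72.40 and 185.34, the critical value is 727.72 and the power is 0.867.

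**Step 2: an exactly correct model.** Multivariate normal data, 12 metrics per marker, no cross-loadings, no residual covariances, no missing data, one homogeneous group. The fit is T = (N − 1)F, with uncorrected RMSEA, CFI and TLI (independence baseline, 630 df) and SRMR; 500 to 1,000 samples per cell at N = 50 and 60.

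Mean T/df is about 1.35 at N = 60 and 1.47 at N = 50, where 1 is expected. Since RMSEA = √[(T/df − 1)/(N − 1)], the average correct model shows √(0.35/59) = 0.077 at N = 60 and √(0.47/49) = 0.098 at N = 50. At loading 0.7 and marker correlation 0.5, mean CFI is 0.83 and SRMR 0.088 at N = 60, and 0.75 and 0.096 at N = 50.

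| Loading | Correct model rejected by the four cut-offs, N = 60 |
|---|---|
| 0.40–0.60 | 100% |
| 0.65–0.70 | 97–100% |
| 0.75 | 90–94% |
| 0.80 | 71–82% |
| 0.85 | 41–43% |
| 0.90 | 37–38% |

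Mixed loadings of 0.4–0.9, 0.5–0.9 and 0.6–0.9 at N = 60 give 99.6%, 98.1% and 91.2%. At N = 50, rejection is 97.4–100% at every loading from 0.40 to 0.95.

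**Step 3: the close-fit test.** Its critical value at N = 60 is 743.77/591 = 1.26 per degree of freedom, below the 1.35 that a correct model averages. It therefore rejects the exactly correct model in 82–91% of samples, depending on the scenario. At N = 50 the threshold is 727.72/591 = 1.23 and rejection is about 100%.

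**Step 4: what helps.**
- Larger N, rule unchanged, marker correlation 0.5: a correct 36-metric model passes at least 80% of the time from about N = 90 (loading 0.7), 120 (0.6), 150–200 (0.5) and 200–300 (0.40).
- Swain correction: multiply T by 1 − [p(2p² + 3p − 1) − q(2q² + 3q − 1)]/[12 × df × (N − 1)], with q = (√(1 + 8 × 75) − 1)/2 = 11.76. The numerator is 97,164 − 3,654 = 93,510, so the factor is 1 − 93,510/418,428 = 0.777 at N = 60 and 1 − 93,510/347,508 = 0.731 at N = 50. RMSEA, CFI and TLI are then met jointly in about 70–100% of samples at N = 60 (loadings 0.6–0.8) and 52–95% at N = 50.
- With SRMR < 0.08 kept, correcting the chi-square still leaves a joint pass rate of only 0–14% at N = 60 for loadings 0.5–0.7 and marker correlation 0.3–0.5. It reaches 79% at loading 0.7 only when the markers correlate at 0.8.

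**The case against.** **Thirty-six metrics is a planning count.** Section 2.8.2 uses exploratory analysis to choose the metrics, and Section 3.2 allows a fallback to the patient's passive data alone. At N = 60, marker correlation 0.5 and loadings 0.6, 0.7 and 0.8, a correct model passes the uncorrected rule in 38%, 69% and 85% of samples with 12 metrics, and in 10%, 43% and 84% with 18. This stands as a limit on scope. It does not remove the point, because the sample size and power are justified only for 36.

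**Loadings could be high.** At N = 60 and loadings of 0.8 or more, rejection is no longer near-certain. Such loadings imply alpha of at least 0.955 per 12-metric marker, which is unlikely for sensor and questionnaire metrics taken from two people, but the document does not exclude them.

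**The daily model may have more rows.** Section 3.1 expects four daily scores per dyad. The calculations take one row per dyad and say nothing about a daily model using four days.

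**The estimator is unnamed.** Uncorrected maximum likelihood is an inference, and a fuller analysis plan might specify otherwise. The cut-offs, p, N and power are nevertheless printed together.

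**Stronger readings.** A reader might infer that the primary objective cannot be answered. The document does not support that: Sections 2.1.1 and 2.8.2 also ask for separation of patient-caregiver from control couples, prediction of the dyad's psychological state, alpha above 0.70 and week-to-week correlation. A reader might also infer that the close-fit test rejects true and false models equally often. That is not shown, since rejection under mediocre fit was not simulated, and the test is not itself one of the four criteria. Finally, the error examined here runs towards failing good models; nothing here shows that bad ones would be validated.

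**Conclusion.** The concern holds for the model on which the study is sized: 36 metrics, three markers, one row per dyad, uncorrected indices. At N = 60 an exactly correct model is rejected in about 90% or more of samples for loadings up to about 0.75. At N = 50 it is rejected in 97% or more at every loading tried. The simulated conditions favour the plan.

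The 94.2% is arithmetically right as a nominal asymptotic figure, given the assumed RMSEA values and level. The same test has a false rejection rate above 80% at N = 60 rather than 5%, so that figure is not evidence that good and mediocre fit can be separated. The conclusion weakens with loadings of 0.8 or more at full recruitment, and with a much shorter list of metrics.

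**What to change.** 1. Compute RMSEA, CFI and TLI from a small-sample-corrected chi-square, for example Swain's.
2. Also replace SRMR < 0.08 with a cut-off simulated under the fitted model at the achieved N and p (the 95th percentile was about 0.08–0.12 in these scenarios), or use a bias-corrected SRMR with its confidence interval. Step 1 alone is not enough.
3. Remove the statement that the criteria guarantee good fit.
4. Describe the 94.2% as a nominal asymptotic figure, or restate it from a simulation or a corrected statistic for the number of metrics actually analysed.

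The cost is a short simulation, some wording and a less favourable stated power; no extra dyads are needed. A prespecified short list of 3–4 metrics per marker is a possible trade-off but not part of the required change: nominal power at N = 60 falls to about 17% with 9 metrics and 25% with 12, and would have to be reported.
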